# Venetoclax combined with low dose cytarabine compared to standard of care intensive chemotherapy for the treatment of favourable risk adult acute myeloid leukaemia (VICTOR): Study protocol for an international, open-label, multicentre, molecularly-guided randomised, phase II trial

**DOI:** 10.1186/s12885-022-10221-2

**Published:** 2022-11-14

**Keywords:** Clinical trial, Acute myeloid leukaemia, Bayesian non-inferiority design, Adaptive design, Venetoclax, Low-dose cytarabine

## Abstract

**Background:**

For patients with acute myeloid leukaemia (AML), the only potentially curative treatment is intensive chemotherapy (IC). This is highly toxic, particularly for patients > 60 years, potentially leading to prolonged hospitalisations requiring intensive supportive care, and sometimes treatment-related death. This also results in extensive healthcare costs and negatively impacts quality of life (QoL). Venetoclax with low-dose cytarabine (VEN + LDAC) is a novel, low-intensity treatment for AML patients who cannot receive IC. VEN + LDAC is given as an outpatient and toxicity appears significantly lower than with IC. Analysis of clinical trials performed to date are promising for patients with the genotype *NPM1*^mut^*FLT3* ITD^neg^, where remission and survival rates appear comparable to those achieved with IC.

**Methods:**

VICTOR is an international, two-arm, open-label, multi-centre, non-inferiority, randomised-controlled phase II trial to assess VEN + LDAC compared to standard of care (IC) as first-line treatment in older patients (initially aged ≥ 60 years) with newly diagnosed AML. The trial will recruit patients with a *NPM1*^mut^*FLT3* ITD^neg^ genotype; those with a favourable risk in relation to the experimental treatment. University of Birmingham is the UK co-ordinating centre, with national hubs in Aarhus University Hospital, Denmark, and Auckland District Health Board, New Zealand. The primary outcome is molecular event-free survival time where an event is defined as failure to achieve morphological complete response (CR) or CR with incomplete blood count recovery after two cycles of therapy; molecular persistence, progression or relapse requiring treatment change; morphological relapse, or; death. Secondary outcomes include cumulative resource use at 12- and 24-months, and QoL as assessed by EORTCQLQ-C30 and EQ-5D-3L at 3-, 6-, 12-, 18- and 24-months. The trial employs an innovative Bayesian design with target sample size of 156 patients aged > 60 years.

**Discussion:**

The principle underpinning the VICTOR trial is that the chance of cure for patients in the experimental arm should not be compromised, therefore, an adaptive design with regular checks on accumulating data has been employed, which will allow for a staged expansion of the trial population to include younger patients if, and when, there is sufficient evidence of non-inferiority in older patients.

**Trial registration:**

EudraCT: 2020–000,273-24; 21-Aug-2020.

ISRCTN: 15,567,173; 08-Dec-2020.

**Supplementary Information:**

The online version contains supplementary material available at 10.1186/s12885-022-10221-2.

## Background

Acute myeloid leukaemia (AML) is an aggressive haematological malignancy, which despite improvements to treatment and supportive care, remains fatal in the majority of patients. The only potentially curative treatment is intensive (or induction) chemotherapy (IC) followed in selected cases by allogeneic stem cell transplantation (SCT) where indicated and when a suitable donor is identified [1, 2]. IC is successful in inducing complete remission (CR) in 60–80% of younger patients (aged 16–60 years) [3, 4] and in around 50% of older patients ≥ 60 years [5, 6]. IC is highly toxic, due mainly to prolonged myelosuppression, which results in a high risk of severe bacterial and/or fungal infection. This is the most frequent cause of induction death, which occurs in 5–10% of patients aged < 60 years [3, 4, 7] and 10–20% of older individuals [7, 8]. Patients undergoing IC are usually hospitalised for a prolonged period and require intensive support with blood products and anti-infective agents, resulting in significant economic cost (estimated a £100,000-£400,000 per patient) and impact on quality of life (QoL) [9–14]. Additionally, patients treated with IC are at risk for several serious long-term side effects including cardiac and neurological sequelae, infertility and secondary cancers [15].

As the risk of mortality with IC increases with age and comorbidity [7, 8] older patients and those with severe pre-existing conditions are typically treated with non-intensive chemotherapy with either low-dose cytarabine (LDAC) or a hypomethylating agent (HMA, i.e., 5-azacitidine or decitabine) [1, 2]. Such treatments, however, display at best modest efficacy resulting in CR in only 10–30% of patients and median overall survival rates of approximately 6–12 months [16–19]. The B-cell lymphoma-2 (BCL2) inhibitor venetoclax (VEN), has been used in combination with LDAC or a HMA in patients not eligible to receive IC. These VEN-based combinations have been shown to produce CR rates between 50–75%, representing a major advance in the treatment of AML [20–22] and leading to the approval of VEN + HMA and VEN + LDAC combination therapy for patients with AML who are ineligible for IC in many countries including the UK [23].

Response to VEN based regimens in AML varies according to the molecular subgroup [24, 25]. The most impressive responses to date have been observed for patients harbouring mutations in *NPM1*, which is the most commonly mutated gene in AML accounting for approximately one third of cases. In this group, the combined phase II data (*n* = 27) demonstrate an overall response rate of 93% and two-year overall survival rate of 75% [20–22, 24, 25], moreover it appears that those *NPM1* mutated patients who do not respond to or who relapse shortly after treatment with VEN based combination therapy usually harbour the *FLT3* internal tandem duplication (ITD) [24].

The rate and durability of response to VEN based combinations in single arm studies for patients with *NPM1* mutated AML compares favourably with outcomes of patients treated with IC, for example adults with the favourable risk genotype *NPM1*^mut^
*FLT3* ITD^neg^ treated with IC in the intensive therapy arm of UK NCRI AML16 (median age 67 years, range 60–84 years) demonstrated overall survival rates at 2 and 3 years of 50% and 35% [26]. These data raise the possibility that the novel non-intensive combination VEN + LDAC may be equivalent or superior to IC in terms of disease-free survival, treatment-related mortality and QoL for patients with *NPM1* mutated AML who currently receive intensive therapy.

The VICTOR trial will, therefore, compare VEN + LDAC to standard of care IC as first-line treatment in older patients (initially aged ≥ 60 years) with de-novo AML with the genotype *NPM1*^mut^
*FLT3* ITD^neg^.

## Design

### Study design

The VICTOR trial is an international, two-arm, multicentre, non-blinded, randomised-controlled phase II clinical trial of VEN + LDAC compared to standard of care IC (daunorubicin, cytarabine and gemtuzumab ozogamicin (DAGO)) in adult AML patients. VICTOR is adaptive trial allowing a staged expansion of the population to include younger patients as evidence emerges of non-inferiority in the older patients. The trial will recruit patients with the *NPM1*^*mut*^* FLT3* ITD^neg^ genotype (Fig. 1) as these have a favourable risk in relation to the experimental treatment. University of Birmingham is the UK co-ordinating centre, with national hubs in Aarhus University Hospital, Denmark, and Auckland District Health Board, New Zealand. The trial is designed to determine if there is sufficient evidence that VEN + LDAC is non-inferior and potentially beneficial compared to IC to warrant further research in a phase III trial. The trial has a Bayesian design with target sample size of 156 patients in the > 60 age group.

**Fig. 1 Fig1:**
[figure not shown]
VICTOR trial schema VICTOR trial schema showing the patient pathway highlighting treatment decisions depending on disease status. #, cycles; CR, complete remission/response; DA, daunorubicin; DAGO, daunorubicin, cytarabine and gemtuzumab ozogamicin; FLAG-IDA, fludarabine, cytarabine and idarubicin; HIDAC, high-dose cytarabine; LDAC, low-dose cytarabine; MRD, minimal residual disease; R, randomisation; VEN, venetoclax

Randomisation will be 1:1 performed electronically using a computer program developed by the Cancer Research UK Clinical Trials Unit (CRCTU), Birmingham, UK. Stratification variables are:Age (60–69 years versus 70 + years (a further variable of 50–59 years to be included when/if required))SexPerformance status (0 versus 1 and 2)

This trial aims to recruit patients at participating centres following referral for suspected AML or at multi-disciplinary team meetings allowing referral to the trial site from other centres in the UK, Denmark, and New Zealand. Recruitment will be over two years, with participants followed up for at least two years. A list of the VICTOR trial centres can be requested from the VICTOR Trial Office ([contact]). The Standard Protocol Items: Recommendations for Intervention Trials (SPIRIT) checklist is provided as Supplementary Appendix 1 [27]. The World Health Organization (WHO) Trial Registration Data Set is provided in Supplementary Appendix 2.

### Patient and public involvement

Two patient representatives, [name] and [name], co-developed the VICTOR Trial protocol by reviewing and refining the protocol, participant-facing documents and providing input into the statistical design of the study, particularly regarding selection of the pre-specified non-inferiority margin. As members of the trial management group (TMG) they will assess study conduct, will be involved in review of any amendments, and will support dissemination of the study results through existing advocacy activities and through social media channels.

### Patient selection

The key eligible criteria are listed in Table 1.

**Table 1 Tab1:** Key patient eligibility criteria for the VICTOR trial

Inclusion Criteria
• Diagnosis of CD33 positive AML • Age ≥ 60 years (prior to the interim analyses performed after enrolment of 50 and 100 patients) • Genotype *NPM1*^mut^ *FLT3* ITD^neg^ (*FLT3*- Tyrosine Kinase Domain mutation, TKD, is permitted) • Considered fit for intensive chemotherapy with anthracyclines by treating physician • Eastern Cooperative Oncology Group (ECOG) performance status 0–2 • Serum creatinine ≤ 1.5 × ULN (upper limit of normal) • Serum alanine aminotransferase (ALT) and aspartate aminotransferase (AST) ≤ 2.5 ULN and bilirubin ≤ 2 × ULN • Able to provide written informed consent
**Exclusion Criteria**
• Previous chemotherapy for AML or any antecedent haematological condition, with the exception of hydroxycarbamide to control white blood cell count • Other active malignancy requiring treatment • Newly diagnosed or uncontrolled HIV or hepatitis B or C infection. Patients with known chronic infections may enrol if the last two tests for viral load have been negative and their current therapy does not include a protease inhibitor or a non-nucleoside reverse-transcriptase inhibitor • Pregnant and lactating patients (patients of childbearing potential must have a negative pregnancy test prior to study entry) • Females of childbearing potential, and their partners, not willing to use adequate contraception during and for up to 7 months after treatment • Patients who are unable to swallow tablets whole • Known hypersensitivity to any of the investigational medicinal products • Patients known to require vaccination with a live vaccine during the treatment period

*AML* acute myeloid leukaemia, *ULN* upper limit of normal

### Screening and consent

It is the responsibility of the investigator to obtain written informed consent for each patient prior to performing any trial related procedure in compliance with national regulations. Country specific patient information sheets (PIS) are provided to facilitate this process. The study has two PIS – one to allow collection of a blood sample to be sent for rapid molecular screening in order to confirm eligibility and the main trial PIS with full study information which should only be provided to the patient only once the genotype is identified as *NPM1*^mut^
*FLT3* ITD^neg^. Research nurses or specialist registrars are permitted to obtain informed consent for the blood sample collection and rapid molecular screening; however only Investigators may obtain consent for the main study. Supplementary Appendix 3 contains the exemplar VICTOR trial informed consent forms, with Supplementary Appendix 4 the PIS.

During screening, patients will be registered and a peripheral blood sample then sent to the trial laboratory at Guy’s Hospital (for patients in the UK and Denmark) or Auckland (for patients in New Zealand) for rapid molecular screening to test for the eligible genotype *NPM1*^*mut*^* FLT3* ITD^neg^. Patients will only be randomised if the eligible genotype is confirmed.

### Interventions

In both arms, cycles are up to 42 days in duration; this includes a 28-day treatment cycle with days 29–42 to allow for neutrophil and platelet count recovery. Patients will be assessed for response after each cycle of treatment once counts have recovered for the first 4 cycles, and subsequently every 3 cycles from cycle 6 onwards. The permitted dose schedules for both arms are described in Table 2.

**Table 2 Tab2:** Permitted treatment schedules within the VICTOR trial

Drug	Dose	Method	Day of Cycle
**Standard of Care (DAGO) Arm ***			
**Cycle 1** (inpatient or ambulatory care setting) **			
Daunorubicin	60 mg/m^2^	1 h IV infusion	1, 3, 5
Cytarabine	100 mg/m^2^ (total 20 doses)	12-hourly by IV push	1–10
Gemtuzumab ozogamicin	3 mg/m^2^ (capped at 5 mg^#^)	2-h IV Infusion	1, 4 (or 4, 7)†
**Cycle 2** (inpatient or ambulatory care setting) **			
Daunorubicin	50 mg/m^2^	1 h IV infusion	1, 3, 5
Cytarabine	100 mg/m^2^ (total 16 doses)	12-hourly by IV push	1–8
**Cycles 3 and 4** (may be given as outpatient, ambulatory care setting or inpatient, as per local practice)			
Cytarabine			
< 60 years	3 g/m^2^ twice a day	12-hourly by IV push	1, 3, 5
60–69 years	1.5 g/m^2^ twice a day	12-hourly by IV push	1, 3, 5
≥ 70 years	1 g/m^2^ once daily	12-hourly by IV push	1–5

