The FLAG-Ida regimen is recommended for salvage therapy as detailed below and adjusted according to the patient’s age as follows (although the final decision on salvage regimen will be made by investigators, taking into account performance status and other co-morbidities).Age < 60: Fludarabine 30 mg/m^2^ (D1-5), cytarabine 2000 mg/m^2^ (D1-5) and idarubicin 8 mg/m.^2^ (D3-5)Age 60–69: Fludarabine 30 mg/m^2^ (D1-5), cytarabine 1000 mg/m^2^ (D1-5) and idarubicin 8 mg/m.^2^ (D3-5)Age ≥ 70: Fludarabine 25 mg/m^2^ (D1-5), cytarabine 1000 mg/m^2^ (D1-5) and idarubicin 5 mg/m.^2^ (D3-5)

Granulocyte-colony stimulating factor is given daily on days 1–5 and then from day 10 until neutrophil count recovery (> 1.0 × 10^9^/L) for all patients. Supportive care should be given according to local guidelines for this regimen which should include prophylaxis for *Pneumocystis pneumonia*.

In the following circumstances, the VICTOR trial allows for patients randomised to receive standard of care (DAGO) to crossover to receive VEN + LDAC treatment for up to 12 cycles:Any patient who meets criteria to receive salvage chemotherapy, but is judged by the investigator to be unfit to receive this for any reason.Any patient who has received salvage chemotherapy and meets criteria to receive a transplant but cannot receive this because of comorbidity, performance status or donor availability.Any patient who has received salvage chemotherapy but who experiences molecular progression.Any patient who has received a transplant and experiences molecular persistence, molecular progression or molecular relapse.

Patients who crossover will be followed up for all trial outcome measures; the occurrence of molecular complete remission after crossover, molecular event-free survival time and overall survival time from crossover will be reported descriptively in this single cohort of patients. The VICTOR schedule of events has been included in Supplementary Appendix 5.

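### Table 2 gives two different dosing frequencies for control-arm cytarabine in cycles 3 and 4 at age 70 or over; the Method cell is probably the wrong one

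*Protocol article*

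**What the plan says.** The Interventions section of the protocol article states: "The permitted dose schedules for both arms are described in Table 2". In the control-arm part of that table, cytarabine for cycles 3 and 4 is set by age band, with separate columns for dose, method and days.

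- Under 60 years: 3 g/m2 twice daily, 12-hourly, days 1, 3 and 5.
- 60–69 years: "1.5 g/m^2^ twice a day", 12-hourly, days 1, 3 and 5.
- 70 years or over: "1 g/m^2^ once daily" in the Dose column, "12-hourly by IV push" in the Method column, days 1–5.

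The control-arm heading carries a footnote that lets treatment follow local practice. It does not say which frequency the table intends. No other part of the article restates the schedule for patients aged 70 or over in these cycles.

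**The concern.** The two younger rows are consistent, since two doses a day and 12-hourly mean the same thing. The oldest row is not. A reader who follows the Dose cell gives one dose a day, and a reader who follows the Method cell gives two.

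What is at stake is patient safety. The possible error is an overdose, and it falls on the oldest patients in the intensive arm. The Background gives the reason for caution: "As the risk of mortality with IC increases with age and comorbidity". Patients aged 70 or over are a planned part of the trial, because that age group is one of the randomisation strata.

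**Working it through.** **Inputs.** All come from the Interventions section of the protocol article: Table 2, control arm, and the salvage regimen described after it.

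**Step 1: what 12-hourly means in this table.** Cycles 1 and 2 state the number of doses, so the meaning can be checked as doses = doses per day × days.

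- Cycle 1, "100 mg/m^2^ (total 20 doses" over days 1–10: 2 × 10 = 20, as stated.
- Cycle 2, "100 mg/m^2^ (total 16 doses" over days 1–8: 2 × 8 = 16, as stated.

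So 12-hourly is two doses a day.

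**Step 2: cytarabine per cycle in cycles 3 and 4.** The formula is dose × doses per day × days.

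| Age band | Reading | Calculation | g/m2 per cycle |
|---|---|---|---|
| < 60 | as printed | 3 × 2 × 3 | 18 |
| 60–69 | as printed | 1.5 × 2 × 3 | 9 |
| ≥ 70 | Dose column, once daily | 1 × 1 × 5 | 5 |
| ≥ 70 | Method column, 12-hourly | 1 × 2 × 5 | 10 |

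The two readings of the last row differ by a factor of 10 / 5 = 2. Over cycles 3 and 4 together they give 2 × 5 = 10 or 2 × 10 = 20 g/m2.

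**Step 3: which cell is more likely wrong.**

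- *Wording.* The dose wording changes to once daily in this row alone, and the days change with it, from 1, 3 and 5 to 1–5. The method text is identical in every control-arm cytarabine row. That is what one would expect if the method had been copied down and not adjusted.
- *Order by age.* With once daily the dose falls with age: 18, 9, 5. With 12-hourly it would run 18, 9, 10, so the oldest group would receive 10 / 9 = 1.11 times the dose given at 60–69 years.
- *Salvage regimen.* For age 70 or over it lists "Fludarabine 25 mg/m^2^ (D1-5), cytarabine 1000 mg/m^2^ (D1-5". If that is one dose a day (no frequency is stated), it gives 1 × 5 = 5 g/m2, the same as the once-daily reading and half the 12-hourly one. This support is weak. Salvage is a different regimen, and the cytarabine listed there for 60–69 years is the same 1000 mg/m2, so it does not step down at 70.

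The first two points carry the inference, and it stands without the third.

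**The case against.** The best counter-argument is that the row nearly resolves itself. In the cycles 3 and 4 block the Dose column carries the frequency in every row, and for this age group it says once daily. A clinician would have to disregard that and take the frequency from the route column to give a double dose. The control-arm footnote also leaves administration to local practice. In addition, this is a journal article published in November 2022 for a trial that opened in June 2021, so sites were already treating under a full protocol that is not shown and may not contain the slip. Only control patients aged 70 or over who reach cycle 3 could be exposed.

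Much of this stands as to weight. Once daily is the better reading, and the error may never have reached a patient. The article alone cannot show that sites prescribe from this table.

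None of it removes the contradiction. The footnote does not choose between the two frequencies, and the article presents Table 2 as the description of the permitted schedules. Condensing a protocol explains omissions, but this is a conflict between two statements that are both printed. A merged cell in the source table would not help either, because 12-hourly would still apply to a once-daily row.

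**Conclusion.** The row contradicts itself as written. It gives 5 g/m2 of cytarabine per cycle by the Dose column and 10 g/m2 by the Method column, a twofold difference in the oldest control-arm age group. That follows from the table alone.

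That once daily is intended is an inference. It is well supported by the wording and by the fall in dose with age, but the article does not say so outright, and the clinical team has to confirm it.

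The point is limited to dosing clarity and safety. No effect on molecular event-free survival, on the treatment comparison or on the sample size is claimed, and no number of affected patients. If sites already give the drug once daily, practice does not change. The correction should still be made, because the misreading runs towards overdose and the change is small.

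**What to change.** 1. Ask the clinical team to confirm that cytarabine in cycles 3 and 4 is given once daily at age 70 or over.
2. In Table 2, change the Method cell of that row from 12-hourly to once daily, with the intended intravenous route.
3. Check the same row in the full protocol. If it carries the same wording, correct it there and notify sites.

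The cost is one clinical confirmation and one table cell, made as a correction to the published article. A site notice is needed only if the full protocol is affected. The footnotes, sample size, analysis set and analysis stay as they are.

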**Venetoclax and Low-dose Cytarabine Arm**			
**Cycle 1** (inpatient^α^)			
Cytarabine	20 mg/m^2^	Subcutaneous^β^	1–10
Venetoclax	100 mg	Oral	1
	200 mg	Oral	2
	400 mg	Oral	3
	100 mg	Oral	4–28
**Cycles 2–4** (outpatient (up to 12 cycles may be given))			
Cytarabine	20 mg/m^2^	Subcutaneous^β^	1–10
Venetoclax^γ^			
Either	100 mg	Oral	1–28
Or	600 mg	Oral	1–28
Accompanying supportive care (one of the following is mandated during all cycles):			
Aciclovir	400 mg twice a day	Oral	1–28
Valaciclovir	500 mg once a day	Oral	1–28
Posaconazole	300 mg twice a day	Oral	4
	300 mg once a day		5–28
Voriconazole	400 mg twice a day	Oral	4
	200 mg twice a day		5–28
Optional supportive care (one of the following is permitted):			
Ciprofloxacin	500 mg twice a day		1–28
Levofloxacin	500 mg once a day		1–28

^*^ May be administered as per local practice

^**^ If current standard of care is treatment in ambulatory care setting or outpatient day unit, this is permitted at the discretion of the treating investigator

^#^ Unless local standard practice is to dose cap at 4.5 mg

^†^ Gemtuzumab ozogamicin (GO) should be given on days 4 and 7 if white blood cell count ≥ 30 × 10^9^/L on day 1. For New Zealand sites standard of care will consistent of daunorubicin and cytarabine only until GO is available for use

^α^ Patients should generally be admitted to hospital for cycle 1 of treatment unless there are established local protocols for ambulatory management of induction therapy

^β^ Method of administration may be as per local practice, including self-administration

^γ^ 100 mg dose used if patient remains on anti-infective prophylaxis, 600 mg if patients stop anti-infective prophylaxis

Following cycle 1 the starting criteria for each cycle (cycle 2–4 of DAGO and cycle 2–12 of VEN + LDAC) are a neutrophil count > 1.0 × 10^9^/L and a platelet count > 75 × 10^9^/L. The subsequent cycle may be delayed by a further two weeks until the counts recover, however, if not recovered six weeks after the start of the preceding cycle (i.e., by day 42), a bone marrow aspirate and trephine will be performed to confirm a morphological leukaemia free state (MLFS). If confirmed, and in the absence of molecular progression, a further delay in treatment may be recommended after discussion with the clinical co-ordinators. If a MLFS is not confirmed, patients may receive salvage chemotherapy.

The FLAG-Ida regimen is recommended for salvage therapy as detailed below and adjusted according to the patient’s age as follows (although the final decision on salvage regimen will be made by investigators, taking into account performance status and other co-morbidities).Age < 60: Fludarabine 30 mg/m^2^ (D1-5), cytarabine 2000 mg/m^2^ (D1-5) and idarubicin 8 mg/m.^2^ (D3-5)Age 60–69: Fludarabine 30 mg/m^2^ (D1-5), cytarabine 1000 mg/m^2^ (D1-5) and idarubicin 8 mg/m.^2^ (D3-5)Age ≥ 70: Fludarabine 25 mg/m^2^ (D1-5), cytarabine 1000 mg/m^2^ (D1-5) and idarubicin 5 mg/m.^2^ (D3-5)

Granulocyte-colony stimulating factor is given daily on days 1–5 and then from day 10 until neutrophil count recovery (> 1.0 × 10^9^/L) for all patients. Supportive care should be given according to local guidelines for this regimen which should include prophylaxis for *Pneumocystis pneumonia*.

In the following circumstances, the VICTOR trial allows for patients randomised to receive standard of care (DAGO) to crossover to receive VEN + LDAC treatment for up to 12 cycles:Any patient who meets criteria to receive salvage chemotherapy, but is judged by the investigator to be unfit to receive this for any reason.Any patient who has received salvage chemotherapy and meets criteria to receive a transplant but cannot receive this because of comorbidity, performance status or donor availability.Any patient who has received salvage chemotherapy but who experiences molecular progression.Any patient who has received a transplant and experiences molecular persistence, molecular progression or molecular relapse.

Patients who crossover will be followed up for all trial outcome measures; the occurrence of molecular complete remission after crossover, molecular event-free survival time and overall survival time from crossover will be reported descriptively in this single cohort of patients. The VICTOR schedule of events has been included in Supplementary Appendix 5.

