### Dose modifications and discontinuations

Recommended dose modifications are listed in Table 3.

**Table 3 Tab3:** Recommended dose modifications within the VICTOR trial

Standard of Care (DAGO) Arm	
**Observation**	**Recommended Modification**
Serum creatinine (mmol/L)	Daunorubicin dose
< 105	100%
105–265	75%
> 265	50%
Bilirubin > 2 × ULN and AST/ALT > 2.5 × ULN	Postpone gemtuzumab ozogamicin dose until less than these levels. Consider omitting the scheduled dose if delayed more than 2 days between sequential infusions
Bilirubin (μmol/L)	Daunorubicin dose
< 20	100%
20–50	75%
> 50	50%
Bilirubin (μmol/L)	Cytarabine dose
> 34	50%

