**Venetoclax and Low-dose Cytarabine Arm**	
During venetoclax maintenance:	
Upon reoccurrence of grade 3 or 4 non-haematological toxicity, or grade 4 haematological toxicities, except lymphopenia	
**Dose at interruption (mg)**	**Restart dose (mg*)**
400	300
300	200
200	100
100	50**

^*^ The modified dose should be continued for 1 week before increasing the dose

^**^ As the venetoclax is only available in 100 mg strength, if a dose reduction to 50 mg is required, the patient should take 100 mg every other day

*ALT* alanine aminotransferase, *AST* aspartate transaminase, *ULN* upper limit of normal

If signs and symptoms of veno-occlusive disease or sinusoidal obstruction syndrome occur in patients treated with gemtuzumab ozogamicin (GO), defibrotide treatment can be considered and GO should be discontinued.

For patients receiving VEN and experiencing grade 3–4 abnormal liver function tests VEN and any potentially hepatotoxic drugs (including azole antifungals) should be withheld until these have resolved to grade 2 or below. Venetoclax (and the azole antifungal if applicable) should be restarted at the original dose. During maintenance, venetoclax may be withheld for any grade 3 or 4 non-haematological toxicity, or grade 4 haematological toxicities (except lymphopenia). Once the toxicity has resolved to grade 1 or baseline level (recovery), therapy with VEN may be restarted at the same dose. If the toxicity recurs, and for any subsequent occurrences, the dose reduction guidelines in Table 3. For patients who require dose reductions to less than 100 mg for more than 2 weeks, discontinuation of VEN should be considered.

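### Two dosing rules in Table 2 contradict themselves (venetoclax 100/600 mg; cytarabine at age 70 and over), and Table 3 gives the creatinine cut-offs in the wrong unit

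*Protocol article*

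**What the plan says.** **Venetoclax (Interventions, Table 2, VEN + LDAC arm).** From cycle 2 the table permits 100 mg or 600 mg on days 1–28. The footnote that decides between them reads "100 mg dose used if patient remains on anti-infective prophylaxis, 600 mg if patients stop anti-infective prophylaxis". Lower in the same table, aciclovir, valaciclovir, posaconazole and voriconazole are listed as supportive care with the instruction "one of the following is mandated during all cycles". The text under Table 3 on liver toxicity says "Venetoclax (and the azole antifungal if applicable) should be restarted at the original dose".

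**Cytarabine (Table 2, standard-of-care arm, cycles 3 and 4).** For age 70 and over, the dose column reads "1 g/m^2^ once daily" and the schedule is days 1–5, but the method column gives a 12-hourly push. For age 60–69 the dose column reads "1.5 g/m^2^ twice a day" on days 1, 3 and 5. A footnote to the whole arm adds "May be administered as per local practice".

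**Creatinine (Dose modifications and discontinuations, Table 3).** The daunorubicin reduction is headed "Serum creatinine (mmol/L" and gives 100% below 105, 75% from 105 to 265 and 50% above 265. The bilirubin rows of the same table are in µmol/L.

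**The concern.** Each item is an operative treatment rule, and the printed rule differs from what was apparently meant.

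- **Venetoclax.** All four mandated drugs are anti-infectives. A patient who follows the mandate is always on anti-infective prophylaxis, so the condition for 600 mg is never met. A patient who stops the azole and keeps aciclovir satisfies the mandate and, on the literal wording, stays on 100 mg.
- **Cytarabine.** One row gives two dosing frequencies that differ by a factor of two. It applies to patients aged 70 and over, who form one of the two initial age strata for randomisation.
- **Creatinine.** In the printed unit the cut-offs lie far outside any patient's range, so the renal reduction of daunorubicin can never apply.

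At stake are correct dosing and consistent delivery of treatment in both arms. The primary outcome, sample size and decision rule are not affected.

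**Working it through.** **1. What 12-hourly means in this table.** Cycle 1 cytarabine is "100 mg/m^2^ (total 20 doses") over days 1–10, and cycle 2 is 16 doses over days 1–8.

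- 20 / 10 = 2 doses a day
- 16 / 8 = 2 doses a day

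The table's own counts are reproduced, so 12-hourly means twice a day.

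**2. Cytarabine per cycle, cycles 3 and 4** (dose × doses per day × days, inputs from Table 2):

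| Age | Reading | Calculation | g/m² per cycle |
|---|---|---|---|
| < 60 | as printed | 3 × 2 × 3 | 18 |
| 60–69 | as printed | 1.5 × 2 × 3 | 9 |
| ≥ 70 | once daily | 1 × 1 × 5 | 5 |
| ≥ 70 | 12-hourly | 1 × 2 × 5 | 10 |

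Once daily keeps the totals falling with age (18, 9, 5). The 12-hourly reading gives the oldest group more than those aged 60–69 (10 against 9). Once daily is therefore the likely intent.

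**3. Venetoclax per 28-day cycle.**

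- 100 × 28 = 2,800 mg
- 600 × 28 = 16,800 mg, a sixfold difference

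This is the planned gap between two permitted doses, not a measured dosing error. It matters for a patient on an antiviral without an azole, who gets the lower dose on the literal reading and the higher one on the apparent intent. Two features of the article point to the azole as the trigger. In cycle 1 the azoles start on day 4, the day venetoclax falls from 400 to 100 mg. The liver-toxicity text treats the azole as something a patient may or may not be taking. Tying the dose to azole use makes both branches reachable; the printed footnote does not.

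**4. Creatinine.** 105 mmol/L equals 105,000 µmol/L. As printed, every patient falls below 105 and receives 100% daunorubicin.

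Read as µmol/L, the rule can affect eligible patients. Table 1 admits creatinine up to 1.5 × ULN.

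- The entry limit exceeds 105 when ULN > 105 / 1.5 = 70 µmol/L.
- It would exceed 265 only when ULN > 265 / 1.5 ≈ 177 µmol/L.
- The article gives no ULN. For an assumed ULN of 80–110 µmol/L, the entry limit is 120–165 µmol/L, inside the 75% row.

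Full daunorubicin in cycle 1 is 60 × 3 = 180 mg/m²; at 75% it is 135 mg/m².

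**The case against.** The strongest reply is that this is a journal article published in November 2022 for a trial that opened in June 2021. Sites were already treating under a full protocol that is not shown, and nothing indicates that anyone doses from the article or that the full protocol repeats the slips. That stands: no misdosing is shown, and the number of patients affected is unknown.

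On venetoclax, it can be argued that the footnote is only ambiguous. The drug list is headed as supportive care, not as anti-infective prophylaxis, and the 600 mg row would be pointless unless the term had a narrower sense. The azole reading is indeed plausible. However, the footnote names no agent, and all four mandated drugs fit its wording, so the reader has to supply the rule.

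On cytarabine, the method entry looks like a cell repeated down the column, the dose column is clear, and the standard arm may follow local practice. This makes a 10 g/m² cycle unlikely in practice. It does not remove the contradiction, because the local-practice footnote does not say which frequency the protocol means.

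On creatinine, a clinician would recognise an impossible unit, and the modifications are only recommendations. That lowers the risk but does not make the heading right. A character lost when the PDF was read is an unlikely explanation, since µmol/L appears correctly for bilirubin in the same table.

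**Conclusion.** The concern holds for all three items: as printed, the text is wrong or self-contradictory. The sizes are 2,800 or 16,800 mg venetoclax per cycle for a patient on an antiviral without an azole, 5 or 10 g/m² cytarabine per cycle at age 70 and over, and a daunorubicin renal reduction that never applies. In the last case an eligible patient could be due 135 rather than 180 mg/m² in cycle 1, which rests on the assumed ULN of 80–110 µmol/L.

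The likely intent can be inferred in each case, but for venetoclax it needs confirmation by the clinical team. These points should be fixed because they are treatment rules and the correction is nearly free. They do not bear on the validity of the planned analysis.

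**What to change.** After checking the full protocol:

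1. Restate the venetoclax footnote by agent. The apparent rule is 100 mg with posaconazole or voriconazole and 600 mg without an azole, to be confirmed by the clinical team.
2. Remove the 12-hourly entry from the cytarabine row for age 70 and over, if once daily is intended.
3. Change the creatinine unit in Table 3 to µmol/L.

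A minor check: the venetoclax reduction ladder in Table 3 starts at 400 mg, so confirm that the full protocol covers a patient interrupted at 600 mg.

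The cost is a short correction to Tables 2 and 3, with no change to sample size, margin or decision rule.
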